### Data collection

Prescription data, process-of-care measures and patient-reported outcomes will be collected at baseline and on intervention completion, that is, the point at which all ten reviews have been completed (this must be within a 6 to 8 week period). Follow-up data will also be collected 12 months after the intervention completion. Data will be collected from the following sources:

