### Intervention

The intervention consists of academic detailing, medicines review with web-based pharmaceutical treatment algorithms and tailored patient information leaflets. The academic detailing will involve a research pharmacist visiting intervention GPs in their own practices. The visit will include a short educational presentation about PIP as a concept, the criteria used to measure it and a summary of studies conducted in Irish primary care on the topic, as knowledge of PIP may be a barrier to appropriate prescribing in older patients [34]. Subsequent to this, practices will be asked to complete ten medicines reviews within a 6 to 8 week period, with a reminder issued if they are not completed within that period. An extended period may be negotiated, should a practice require it. During the medicines review, the GPs will use web-based treatment algorithms specifically designed for this study and accessible using a link and designated password. The algorithm will guide the process from the GP perspective, and does not incorporate patient involvement. It has a page-by-page structure, which will be completed when the GP fills in a review outcome form, detailing decisions made by the GP and patient together, including the reasons for maintaining a PIP, which is a key element of this study. Once the review outcome form has been filled in, the medicines review is complete. The medicines review will take place in the GP practice and will be scheduled at a date and time that is convenient to both the GP and the patient. In group practices where more than one GP is participating, the reviews may be divided between them in a manner that is most suitable to the practice workload. The pilot study indicated that the preparation for the review might be more time consuming for the GP than usual but there was no indication that the consultation itself would be significantly longer. These components are presented in Table 1.

**Table 1 T1:** Intervention components

**Intervention component**	**Description**
Academic detailing	A research pharmacist will visit the intervention practices. During the academic detailing, the pharmacist will:
	• Discuss the concept of PIP with the GPs, focusing on the prevalence and consequences of PIP in primary care
	• Discuss the pharmaceutical treatment algorithm
	• Discuss the medicines review process

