### Control group: usual care with simple feedback

The control-group GPs will continue to provide usual care but will also be provided with simple feedback. Data for patients in the control group will be reviewed during recruitment and a personalized patient list for the ten recruited patients will be given to the GP. The list will summarize the medication class to which the individual patient’s potentially inappropriate medication belongs, not the specific PIP and will not provide actionable recommendations for change. Participants will not receive an academic detailing visit, will not be prompted to carry out a medicines review with the individual patients, and will not have access to the pharmaceutical treatment algorithms with alternative therapy options. GPs will continue to provide usual care. In terms of repeat prescribing for public general medical services (GMS) patients, this means that a GP can give a prescription on a monthly basis or for a maximum of three months. At present, the Health Service Executive Primary Care Reimbursement Services (HSE-PCRS) has an on-line GP Application Suite where GPs can review administrative information on their GMS patient panel. They can also access prescribing analysis reports, which contain detailed financial and cost information related to their prescribing. Specific prescribing alerts and recommendations for older patients are not provided.

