Prednisolone (or equivalent) > 3 months or longer without bisphosphonate	Increased risk of fracture	N/A
NSAID with ACE-inhibitor	Risk of kidney failure, particularly with the presence of general arteriosclerosis, dehydration or concurrent use of diuretics	N/A
NSAID with diuretic	May reduce the effect of diuretics and worsen existing heart failure	N/A

ACEI, angiotensin-converting-enzyme inhibitor; COPD, chronic obstructive pulmonary disease; GI, gastro-intestinal; GORD, gastro-oesophageal reflux disease; N/A, not available; NSAID, nonsteroidal anti-inflammatory drug; PPI, proton pump inhibitor; p.r.n., *pro re nata*, as needed; SSRI, selective serotonin reuptake inhibitor; TCA, tricyclic anti-depressant. *Prevalence: the proportion of the study population with one or more potentially inappropriate medications.

The primary outcomes to be determined are the proportion of participant patients with PIP (as a composite measure, that is, any number of PIP criteria as listed in Table 2, to address the issue of multiple PIP in individual patients) and the mean number of potentially inappropriate prescriptions per patient.

Secondary outcomes (summarized in Table 3) will include individual measures of the composite measure, that is, drug-specific outcomes, process evaluations, process-of-care measures and patient-reported outcomes (Health status (EQ-5D) [38], Patients’ Beliefs about Medicine Questionnaire (BMQ) [39], Well-being Questionnaire (WBQ-12) [40]).

**Table 3 T3:** Secondary outcome measures

**Secondary outcome**	**Measure**
Drug-specific outcomes	The absolute number of PIPs per patient of the top five occurring PIP drugs: [11]
	Proton pump inhibitor (PPI) for peptic ulcer disease at full therapeutic dosage for >8 weeks
	Long-term (>3 months) use of NSAIDs for relief of mild joint pain in osteoarthritis
	Long-term (>1 month) use of long-acting benzodiazepines, for example, chlordiazepoxide, flurazepam, nitrazepam, chlorazepate and benzodiazepines with long-acting metabolites for example, diazepam
	Any regular duplicate drug class prescription
	TCAs with an opiate or calcium channel blocker
	Mean number of PIPs per patient of the top five PIP drugs (as above)
Patient-reported outcomes	Health status (EQ-5D)
	Patients’ Beliefs about Medicine Questionnaire (BMQ)
	Well-being Questionnaire (WBQ-12)
Process-of-care measures	Number of GP visits (6 months prior to enrolment and at 4 and 12 month follow-up)

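### Both follow-ups are timed from completion of the medicines reviews, an event control practices do not have, so the arms could be measured after different elapsed times

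*Protocol article*

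**What the plan says.** Under Data collection, prescription data, process-of-care measures and patient-reported outcomes are gathered at baseline and "on intervention completion, that is, the point at which all ten reviews have been completed", with the added condition that "this must be within a 6 to 8 week period". The later collection depends on the same event: "Follow-up data will also be collected 12 months after the intervention completion".

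The Intervention section is softer on the limit. There, "practices will be asked to complete ten medicines reviews within a 6 to 8 week period", a reminder follows if they are late, and "An extended period may be negotiated, should a practice require it". No maximum is given.

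Table 3, under Outcome measures, lists GP visits with the times "6 months prior to enrolment and at 4 and 12 month follow-up", and gives the same times for hospital admissions. It does not say from when the 4 and 12 months run.

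Control practices receive a feedback list and are not prompted to review anyone (Control group section). The Trial design section defines their participation as supplying prescription data, with no date. In the intervention arm, participation means attending the detailing visit and undertaking reviews. Practices that do not meet their arm's definition are treated as lost to follow-up. The definition of the two primary outcomes names no time point.

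**The concern.** Follow-up in a randomised comparison should start from something both arms share. Here the stated starting event exists in one arm only, and within that arm its date depends on how quickly each practice works. Control practices may be given matching dates, but the article states no rule for it.

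This matters more than usual because having PIP is an entry criterion. At baseline the proportion with PIP is 100% by design, so any early background change can only be a fall. If control practices are measured sooner than intervention practices, background change adds to the apparent effect. If they are measured later, it hides some of the effect. The sample size section assumes no improvement in the control arm. The second primary outcome, the mean number of PIPs per patient, is open to the same problem, although its direction of drift is less certain.

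A second consequence concerns missing data. An intervention practice that never finishes its reviews has no defined measurement date, and one that undertakes none is counted as lost to follow-up. A control practice need only send data. Whether outcomes are available then depends on compliance in one arm, which sits badly with the intention-to-treat commitment in the Plan of analysis.

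**Working it through.** **Benchmark.** The article has no figure for timing. Its relevant figure is the target difference of 10 points (100% against 90%), and the sample size built on it can be closely reproduced.
- Inputs (Sample size section): one-sided 5%, 80% power, ICC 0.025, ten patients per practice, 10% loss.
- Per arm, uncorrected: (1.645 × √(2 × 0.95 × 0.05) + 0.842 × √(0.9 × 0.1))² / 0.1² = 57.7. With continuity correction this becomes 77.
- Design effect: 1 + 9 × 0.025 = 1.225.
- Total: 2 × 77 × 1.225 / 0.9 = 209.6, against 212 stated. Per arm 104.8 / 10 = 10.5, so 11 practices, or 22 in all, as stated.

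The 10-point difference is therefore the right yardstick. Nothing in this point disputes the sample size.

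**Timing statements side by side.**

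| Section | First follow-up | Last follow-up | Start point |
|---|---|---|---|
| Data collection | completion of all reviews, mandatory 6 to 8 weeks | 12 months after completion | review completion |
| Intervention | reviews requested in 6 to 8 weeks, extension negotiable, no maximum | not addressed | after the detailing visit |
| Table 3 (GP visits, admissions) | 4 months | 12 months | not stated |
| Any section, control arm | follow-up, no date | follow-up, no date | not stated |

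- At 4.345 weeks per month, 6 to 8 weeks is 1.4 to 1.8 months, and 4 months is 17.4 weeks.
- Completion at 8 weeks plus 12 months is 12 + 1.8 = 13.8 months from the start of the review period, and more with an extension.

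The first two rows conflict as written: a mandatory limit and an open-ended extension cannot both hold. Table 3 may be compatible with Data collection if its months run from an earlier event, but none is named.

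**Illustration of size.** The documents give neither a background rate nor a gap, so both are assumed. If a share h of patients per month lose their last PIP under usual care, starting near 100%, a gap of d months shifts the proportion by 100 × (1 − exp(−h × d)) points. For d = 2:
- h = 0.5%: 1.0 point
- h = 1%: 2.0 points
- h = 2%: 3.9 points
- h = 3%: 5.8 points

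With h = 0, which is what the sample size assumes for the control arm, the shift is zero whatever the gap.

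**The case against.** The strongest reply is that unequal timing is inferred. The article says that chart and questionnaire data come from both arms at baseline and follow-up. Scheduling control practices at matched dates is an operational detail that a full protocol could hold, and the flow chart in Figure 1 is not visible in the text at hand. This stands: a reader might infer that the arms will be measured at different times, but the text shows only that they can be. It does not remove the problem that the one trigger the article states applies to one arm.

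Other stronger readings are not supported either.
- **Table 3 contradicts the primary time point.** Its entry, "Number of GP visits (6 months prior to enrolment and at 4 and 12 month follow-up", and the matching one for admissions concern secondary process-of-care measures only. The look-back in the same cell runs from enrolment. Baseline collection, allocation and detailing come before the reviews, so 4 months from enrolment might be the same occasion as review completion. The 12-month figure is harder to fit. This is an unstated start point, not a proven conflict.
- **The proportion with PIP can only fall.** That is true of the first change from 100%, but not afterwards. Any Table 2 criterion counts, so a patient can relapse or acquire a new PIP before the last follow-up.
- **Measurement comes too early in the repeat cycle to detect change.** Under usual care "a GP can give a prescription on a monthly basis or for a maximum of three months", but outcomes are taken from GP records, where a stop or dose change can be entered at once. The duration thresholds in Table 2 mainly delay the counting of newly started drugs.
- **A practice with fewer than ten patients never reaches its trigger.** This takes the wording too literally; all ten naturally means all recruited patients.

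**Conclusion.** The point holds as a weakness in how measurement time is fixed. Both post-baseline collections are tied to an event in one arm only, no control date or primary time point is stated, and the limit on the review period is given inconsistently. Unequal elapsed time could bias the comparison of both primary outcomes.

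No size can be read from the documents. The range of about 1 to 6 points rests entirely on an assumed two-month gap and assumed loss rates of 0.5% to 3% per month. It shows that a modest gap need not be negligible beside a 10-point target. It is not an estimate of bias in this trial.

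This should be fixed, mainly because the remedy is cheap and unequal measurement times cannot be undone once data are collected. It does not show that the trial's result would be invalid.

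**What to change.** 1. Schedule both follow-ups from the date of practice allocation, with the same target times and windows in both arms, whether or not reviews are complete.
2. Name which follow-up is primary for the two primary outcomes.
3. Collect outcomes from intervention practices that do not undertake or finish reviews, instead of counting them as lost to follow-up under Trial design. Without this, fixed dates alone would leave outcome availability dependent on compliance. The planned per-protocol analysis can still be restricted to those who completed.
4. Reconcile the Intervention section, the Data collection section and Table 3 on the length of the review period and on the start point for 4 and 12 months. Which review period applies is for the trial team to decide.

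The cost is protocol wording, a follow-up calendar set at allocation, and data requests to some non-completing practices. Some late-reviewing practices will be measured before they finish, which slightly dilutes the effect. This point calls for no change to the sample size. The Trial status section reports that patient identification was only just starting, so at that stage no follow-up would have to be repeated.

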#### GP medical chart

Patient records will be used to collect the drug-specific outcome data for all participants at baseline and follow-up. Process-of-care data, such as health-service utilization (for example, the number of GP visits) will also be collected for intervention and control patients.

#### Questionnaire

Patient-reported outcomes for intervention and control will come from questionnaire data, which will be collected at baseline and follow-up, using a postal questionnaire and telephone follow-up for nonresponders. The questionnaire will be used to collect personal and demographic data, economic data, and health-service utilization data along with data from the EQ-5D, BMQ and WBQ-12.

#### Evaluation data

Process-measure data for the intervention group will be collected by outcome forms completed by GPs at the end of each of the ten medicines reviews they conduct for the ten recruited patients. In single-handed practices, the same GP will conduct the reviews and complete the outcome forms. In group practices, where more than one GP is participating in the study, the reviews may either be conducted by an individual GP nominated by the practice or be shared between the GPs, with GPs completing outcome forms for the patients they reviewed. Semistructured qualitative interviews will also be conducted with both GPs and patients after the intervention, to evaluate the intervention (see below for more detail). GPs in the control arm will also be interviewed, to ascertain any potential impact of the feedback they receive, based on the baseline data.

### Plan of analysis

The minimization process will ensure balance between treatment groups in terms of certain prognostic factors. Descriptive statistics will be used to evaluate differences in other baseline characteristics between participating physicians and patients in the two arms of the trial. The primary analysis will be carried out using multilevel modeling (such as mixed linear effects modeling or generalized estimating equations [41]) to control for the effects of clustering and baseline differences. All analysis will be conducted under the intention-to-treat principle.

Subgroup analyses will be performed for the primary outcome to assess whether the intervention varies by practice size or GP characteristics, such as sex or number of PIP drugs. As this is a pragmatic trial, a secondary, per-protocol analysis will also be conducted. This form of analysis includes only those participants who completed the treatment protocol originally allocated, providing results on the efficacy of the trial [42].

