**Methods/design:**

This study is a pragmatic cluster randomized controlled trial, conducted in primary care (OPTI-SCRIPT trial), involving 22 practices (clusters) and 220 patients. Practices will be allocated to intervention or control arms using minimization, with intervention participants receiving a complex multifaceted intervention incorporating academic detailing, medicines review with web-based pharmaceutical treatment algorithms that provide recommended alternative treatment options, and tailored patient information leaflets. Control practices will deliver usual care and receive simple patient-level feedback on potentially inappropriate prescribing. Routinely collected national prescribing data will also be analyzed for nonparticipating practices, acting as a contemporary national control. The primary outcomes are the proportion of participant patients with potentially inappropriate prescribing and the mean number of potentially inappropriate prescriptions per patient. In addition, economic and qualitative evaluations will be conducted.

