### Recruitment and allocation

Potentially eligible practices (based in the greater Dublin area) will be identified from the Health Research Board (HRB) Primary Care Research Centre research network. All eligible practices will be invited to participate by an email (or letter where email address is unavailable), which will include a study information leaflet outlining steps of the intervention and availability of continuing medical education (CME) points for participation. When a practice agrees to participate, a member of staff (for example, a GP, practice manager or nurse) will be selected by the practice. The research team will instruct the designated person on how to identify a random sample of 50 patients aged 70 years and over from the patients of participating GPs within the practice. They will pseudo-anonymize the records by assigning the patients a study ID and send a copy of the pseudo-anonymized prescription records to the research team, where a research pharmacist will generate a list of potentially eligible patients, that is, patients with PIP. A maximum of ten patients per practice is required; if more than ten patients are identified, ten patients will be selected at random from the list of eligible patients. Eligible patients will be sent a letter of invitation, a patient information leaflet and a consent form, asking them to participate and answer a questionnaire. Prior to practice allocation, baseline patient data (including prescription data, process-of-care measures and patient-reported outcomes – see sections on outcomes and data collection) will be collected. Practices will then be assigned to intervention or control using minimization. This approach offers the advantage of ensuring balance between the groups [32] in terms of prognostic factors: in this case, practice size (number of whole-time-equivalent GPs) and practice location (urban or rural, where an urban area is defined as a relatively small centre of population, with 5000 or more residents [33]). A chart of the flow of participants through the study is presented in Figure 1. Because of the nature of the intervention, it is not possible to blind GPs or participants to the intervention.

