#### Proportion of participant patients with PIP

The calculation is based on demonstrating a clinically relevant 10% absolute reduction (from 100% to 90%) in the proportion of PIP with 80% power and a statistical significance of 5% (one-sided), between the randomized groups. With a cluster design, the assumption that individual outcomes are independent of each other does not hold, as participants in the same cluster may respond in the same way. The sample size, therefore, needs to be adjusted to reflect this by use of the intraclass correlation coefficient (ICC) [43]. We used an ICC of 0.025, based on an ongoing unpublished observational study of an elderly cohort in the HRB Centre for Primary Care Research. With a maximum of ten patients per cluster and factoring in a loss to follow-up of 10%, a total of 22 GP practices and 212 patients will be required.

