#### Mean number of PIP per patient

An ongoing unpublished observational study of an elderly cohort in the HRB Centre for Primary Care Research estimates a mean number of 1.45 inappropriate prescriptions per patient. To demonstrate a 30% relative reduction in the mean number of PIP (equivalent to a mean of 1.02), with 80% power and a statistical significance of 5% (two-sided), between the randomized groups, with a maximum of ten patients per cluster and factoring in a loss to follow-up of 10%, a total of 14 GP practices and 132 patients will be required.

These calculations indicate that we would need at least 22 practices and 212 patients to detect a difference between the intervention and control arms for both of our primary outcome measures. On the basis of these calculations, we aim to recruit at least 22 practices, with 10 patients per practice, giving a total of 220 patients. With this sample size, we would have at least 80% power to demonstrate a 10% absolute reduction in the proportion of PIP and a 30% relative reduction in the mean number of PIPs. Based on existing evidence that suggests that simple, less intensive feedback does not alter prescribing behaviour [35,36] we have not anticipated an improvement in the control arm. However, we will monitor for this in the parallel process evaluation.

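### GEE is allowed as the primary analysis with only 22 practices; without a small-sample correction its nominal 5% test has about 7.5% type I error

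*Protocol article*

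**What the plan says.** Under Plan of analysis, the primary analysis is to be "multilevel modeling (such as mixed linear effects modeling or generalized estimating equations [41", with the stated purpose of controlling for clustering and baseline differences. The section names no link function, variance estimator, reference distribution or degrees of freedom.

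The trial is described in the abstract as "involving 22 practices (clusters) and 220 patients". The section on recruitment and allocation says "Practices will then be assigned to intervention or control using minimization"; it states no ratio.

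For the binary primary outcome, the sample size section targets a "clinically relevant 10% absolute reduction (from 100% to 90%) in the proportion of PIP". The test there is one-sided at 5%, and power is set at 80%. It uses an ICC of 0.025, at most ten patients per practice and 10% loss, and concludes that "a total of 22 GP practices and 212 patients will be required". All patients have PIP at entry by selection, and no improvement is anticipated in the control arm. The second primary outcome, the mean number of PIP, is planned at 5% two-sided.

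**The concern.** The protocol gives GEE as one acceptable route to the primary result. The standard GEE sandwich variance is justified when the number of clusters is large. With 11 per arm it is biased downwards, and a normal reference ignores that the between-practice variance is estimated on about 20 degrees of freedom. Both faults act in the same direction: standard errors too small, critical value too small. An analyst who took the GEE option with ordinary software defaults would overstate the evidence on both primary outcomes.

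A lesser matter concerns the binary outcome. If a logit link were chosen and the trial turned out as planned, every control patient would still have PIP. The odds ratio would then be infinite and its Wald test unusable.

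**Working it through.** **Inputs.** From the protocol: 22 practices, 10 patients each (about 9 after 10% loss), ICC 0.025, 100% versus 90%, 80% power, 5% one-sided for the proportion and 5% two-sided for the mean. Assumed here: 1:1 allocation (k = 11 per arm), equal cluster sizes, no covariates.

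**1. The plan's own sample size.**
- Per arm, uncorrected: [1.645 × √(2 × 0.95 × 0.05) + 0.8416 × √(1.0 × 0 + 0.9 × 0.1)]² / 0.10² = 0.7595² / 0.01 = 57.7.
- With continuity correction: (57.7 / 4) × [1 + √(1 + 4 / (57.7 × 0.10))]² = 76.4, so 77.
- Design effect 1 + 9 × 0.025 = 1.225: 77 × 1.225 = 94.3, so 95.
- Loss: 95 / 0.9 = 105.6, so 106 per arm, 212 in total, 11 practices per arm.

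This matches the stated 22 practices and 212 patients, and supports reading the design as 11 per arm.

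**2. Type I error of uncorrected GEE, analytically.** With equal cluster sizes and no covariates, the sandwich variance divides the between-practice sum of squares by k instead of k − 1. It is therefore too small by the factor 10/11, and the standard error by √(10/11) = 0.953. The correctly scaled statistic is approximately t on 2 × 11 − 2 = 20 df.
- Two-sided: P(|t₂₀| > 1.96 × 0.953) = P(|t₂₀| > 1.869) = 7.6%.
- One-sided: P(t₂₀ > 1.645 × 0.953) = P(t₂₀ > 1.568) = 6.6%.
- Width of the correct 95% interval relative to the uncorrected one: 2.086 / 1.869 = 1.12.

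**3. The same by simulation.** Beta-binomial data, 2 × 11 practices of 9 or 10 patients, no effect, true proportion 0.7 or 0.9, ICC 0.025, 40,000 trials per setting:

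| Method | Two-sided 5% | One-sided 5% |
|---|---|---|
| GEE, uncorrected sandwich, z | 7.4–7.9% | 6.3–6.6% |
| REML linear mixed model, z | 5.1–5.5% | 4.9–5.0% |
| Practice-level t, 20 df | 4.8–5.2% | 4.8–5.0% |

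The GEE excess hardly depends on the ICC: 7.4–7.7% two-sided at ICC 0.05 and 0.10. The mixed model with z moves to 5.6–6.0% at ICC 0.05 and 5.8–6.4% at ICC 0.10. For a normal outcome it gives 5.4% at 0.025 and about 6.1% from 0.05 up to 0.20. A separate run of 1,500 trials with a Poisson count outcome gave 7.5% for uncorrected GEE, so the second primary outcome is affected in the same way.

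**4. Power after correction.** 100% versus 90%, 9 analysed per practice, ICC 0.025:
- t on 20 df: 98% one-sided, 92% two-sided.
- Welch degrees of freedom: 97% and 87%.
- Mixed model referred to t on 20 df: 91% two-sided.

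**5. Logit link in the planned scenario.** With control 110/110 and intervention 99/110, the log odds ratio has no finite maximum. The fitted coefficients ran off to −24 (GEE) and to −19 with a standard error of 3142 (ordinary logistic). An identity-link model on the same data returned −0.10. The chance that no control patient is PIP-free (99 to 110 control patients, ICC 0.025) depends on the true control proportion: certain at 100%, 37–40% at 99%, 13–16% at 98%, about 1% at 95%.

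**The case against.** The strongest reply is that the protocol fixes none of the faulty choices. Its wording offers examples, and the variance estimator, link, effect scale and degrees of freedom are commonly left to a statistical analysis plan, which is not shown here. That stands: their absence is not an error, and nothing in the protocol excludes a corrected variance. It does not remove the point, because GEE is named as a route to the primary result in a 22-practice trial, and its ordinary form is materially anticonservative there.

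A reader might infer three stronger things. None is supported.
- **That mixed models share the fault.** At the protocol's ICC, a REML linear mixed model with a z reference is within about half a percentage point of nominal.
- **That the plan commits to an odds ratio.** No logit link or odds ratio appears in the analysis or sample size sections. For a 0/1 outcome, the coefficient of a linear mixed model is a risk difference, and it is finite at 100% versus 90%.
- **That the main analysis is likely to break down.** Separation requires that no control patient loses a PIP. The 100% is a planning premise, and the protocol says it will monitor for control-arm improvement.

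It is also fair to say that the sample size is not undermined.

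**Conclusion.** The point holds for uncorrected GEE: about 7.5% two-sided and 6.5% one-sided type I error in place of 5%, on both primary outcomes. It does not extend in any important degree to the linear mixed model at ICC 0.025. The logit problem is conditional: certain if that link is chosen and the control arm stays at exactly 100%, and negligible once the control proportion is near 95%.

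The figures assume 1:1 allocation, equal cluster sizes and no covariate adjustment; unequal sizes and adjusted models were not simulated. The analytic result and the simulations agree, so the size of the GEE excess is secure under those assumptions.

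**What to change.** State one primary method for each outcome, in the protocol or the analysis plan:
- If GEE is kept, use a bias-corrected sandwich variance with a t reference on about 20 df.
- Otherwise, use the linear mixed model with small-sample degrees of freedom (for example Kenward-Roger), or practice-level summaries with a t distribution.
- Report the binary outcome as an absolute risk difference, and the count as a difference in mean number of PIP.

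The cost is a sentence or two and standard software options. Intervals widen by about 12% compared with uncorrected GEE. The mixed model referred to a fixed 20 df is slightly conservative at ICC 0.025 (3.8–4.1% two-sided in the simulations). Power at the protocol's inputs stays well above 80%. It would fall short only under a two-sided test with a much larger ICC: 77% at ICC 0.10 with 9 analysed per practice, against 93% at the protocol's one-sided level.
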